## Abstract

**Background:**

Despite improvements in radiation techniques, pelvic radiotherapy is responsible for acute and delayed bladder adverse events, defined as radiation cystitis. The initial symptoms of bladder injury secondary to pelvic irradiation are likely to occur during treatment or within 3 months of radiotherapy in approximately 50% of irradiated patients, and have a significant impact on their quality of life. The pathophysiology of radiation cystitis is not well understood, particularly because of the risk of complications associated with access to bladder tissue after irradiation, which limits our ability to study this process and develop treatments.

**Objective:**

It is an original study combining digital data collection to monitor patients’ symptoms and biological markers during irradiation. The main objective of our study is to evaluate the correlation of biological biomarkers with the intensity of acute radiation cystitis and the quality of life of patients, assessed with the digital telemonitoring platform Cureety.

**Methods:**

Patients with intermediate-risk localized prostate cancer who are eligible for localized radiotherapy will be included. Inflammatory biomarkers will be analyzed in urine and blood samples before the start of radiotherapy and at weeks 4, 12, and 48 of irradiation, through quantitative methods such as a multiplex Luminex assay, flow cytometry, and enzyme-linked immunosorbent assay. We will also characterize the patients’ gut and urine microbiota composition using 16S ribosomal RNA sequencing technology. Between sample collection visits, patients will complete various questionnaires related to radiation cystitis symptoms (using the International Prostate Symptom Score), adverse events, and quality of life (using the Functional Assessment of Cancer Therapy–Prostate questionnaire), using the Cureety digital remote monitoring platform. Upon receipt of the questionnaires, an algorithm will process the information and classify patients in accordance with the severity of symptoms and adverse events reported on the basis of Common Terminology Criteria for Adverse Events and International Prostate Symptom Score standards. This will allow us to correlate levels of urinary, blood, and fecal biomarkers with the severity of acute radiation cystitis symptoms and patient-reported quality of life.

**Results:**

The study started in March 2022. We estimate a recruitment period of approximately 18 months, and the final results are expected in 2024.

**Conclusions:**

This prospective study is the first to explore the overexpression of inflammatory proteins in fluid biopsies from patients with symptoms of acute radiation cystitis. In addition, the 1-year follow-up after treatment will allow us to predict which patients are at risk of late radiation cystitis and to refer them for radioprotective treatment. The results of this study will allow us to develop strategies to limit radiation damage to the bladder and improve the quality of life of patients.

**Trial Registration:**

ClinicalTrials.gov NCT05246774; https://clinicaltrials.gov/ct2/show/NCT05246774?term=NCT05246774

**International Registered Report Identifier (IRRID):**

DERR1-10.2196/38362

## Introduction

### Background and Rationale

Prostate cancer is the leading cancer diagnosed in men in France, with 50,400 new cases and 8100 deaths in 2018. Improved diagnostic strategies and therapeutic management have led to a 3.7% reduction in mortality between 2010 and 2018, and the survival rate is 93% at 5 years and 80% at 10 years [1], resulting in improved overall survival. However, treatment-related adverse events can be significant and have an impact on adherence to treatment, frequency of hospitalization and associated costs, as well as on the health-related quality of life of patients [2].

Radiation therapy (including conventional radiation therapy, stereotactic body radiation therapy, and brachytherapy) is an important therapeutic technique in the management of pelvic cancers, including prostate cancer [3,4]. Despite improvements in radiation techniques, pelvic radiotherapy remains responsible for a number of acute and late bladder adverse events—these symptoms are grouped under “radiation cystitis.” In France, late radiation cystitis affects 9000 to 18,000 patients per year [5].

Early symptoms of radiation cystitis may occur during treatment and up to 3 months after the end of radiotherapy, with an estimated all grade incidence of nearly 50% after pelvic irradiation [5]. These side effects are characterized by frequent and urgent urination during day- and nighttime, a burning sensation during urination (irritative symptoms), and pain. Difficulty in urinating (obstructive symptoms) or, more rarely, blood in the urine (hematuria) may also be present [6]. More rarely, in 5%-10% of cases, complications appear later (more than 6 months after radiotherapy), whether or not they were preceded by early signs [5,7]. Late lesions involve blood vessel damage and fibrosis of the bladder wall, which may progress chronically and lead to bladder atrophy and even retraction in the most extreme cases [5]. Clinical signs vary depending on the dominant clinical form: cystalgia, pollakiuria, bladder hyperactivity, and isolated mictional disorders. In a classic clinical scenario, recurrent hematuria is a predominant symptom, occurring in abundance and with variable frequency, which can potentially progress to urinary retention with bladder clotting. The chronic and recurrent nature of hemorrhagic cystitis often has a considerable impact on the quality of life of patients. The most severe forms can lead to clot formation and acute urinary retention, which can be life threatening [5,7].

Although some factors have been identified, such as the dose received, fractionation and, comorbidities (eg, diabetes and tobacco smoking), the pathophysiology of radiation cystitis remains poorly studied, particularly because of the risks of complications arising from access to the bladder tissue post irradiation, thus limiting our knowledge of and therapies targeting this process*.*

### The Role of Immunity in the Pathomechanism of Radiation-Induced Injury

Immunity plays an important role in the mechanism of radiation-induced toxicity or inflammation [8,9]. During the repair process of radiation-induced injuries, inflammatory cells (macrophages, neutrophils, and lymphocytes) are recruited to the site of injury, which may contribute to late inflammatory tissue diseases through a continuous mechanism involving inflammation, hypoxia, and fibrosis [10]. The balance between M1 and M2 macrophages plays a central role in the fibrotic process, with a polarization toward M1 macrophages in a fibrotic situation [11,12]. Functional tests measuring the apoptosis of CD4^+^ and CD8^+^ T lymphocytes after irradiation found a significant association between these apoptotic lymphocytes and the risk of occurrence of late genitourinary toxicity [13].

The interstitial cystitis model is similar to the radiation cystitis model in terms of not only collagen accumulation but also symptoms. Patients with interstitial cystitis have very severe genitourinary pain, and many are diagnosed with depression and anxiety. A positive correlation between elevated urinary proinflammatory cytokines (interleukin [IL] 4 and macrophage-derived chemokines) and the severity of interstitial cystitis has been reported [14,15].

### Role of the Microbiota in the Pathomechanism of Radiation-Induced Lesions

Evidence of the protection of microbial communities, especially in the gastrointestinal tract, has led to investigations of the role of the human microbiota in patient health and well-being [16,17].

Radiation therapy to the prostate causes a disruption in the composition of the microbiota, which may promote gastrointestinal toxicities through altered gut barrier function and inflammation [18,19]. It has been shown that the gut microbiota of patients with pelvic cancers who have had radiotherapy is less diverse than that of patients who have not been irradiated [18]. Wang et al [19,20] reported that pelvic radiotherapy is associated with dysbiosis characterized by a decrease in α-diversity in favor of β-diversity. In order to reduce the digestive disorders induced by pelvic radiotherapy, an approach based on fiber supplementation in patients (partially hydrolyzed guar gum) has proven to be effective in reducing diarrhea induced by radiotherapy and has allowed the improvement of the bacterial load of the microbiota while improving nutritional status and the quality of life of patients with cancer [21]. However, the numbers considered in Bull et al’s [21] study were limited. Another study [22] also considered fecal microbiota transfer as a therapeutic solution to slow the spread of radiation-related symptoms—this approach showed encouraging signals for reducing the symptoms of hematuria and diarrhea.

Biomarkers based on the urinary microbiota may represent new diagnostic, prognostic, and therapeutic tools for functional disorders of the lower urinary tract. It has been shown that the urinary microbiota of patients with interstitial cystitis is less diverse than that of patients without these symptoms [20].

To date, no study has evaluated the modification of the urinary microbiota in patients with radiation cystitis. A better understanding of the impact of the urinary microbiota on the etiopathogenesis of urological disorders may help optimize medical management.

It is also important to note that the microbiota of different organs are linked. It is known that the gut microbiota is capable of changing its microbial composition, and these changes can affect the urinary microbiota [21].

### Main Objective

The main objective of this study is to determine inflammatory and remodeling markers involved in the occurrence of early (<3 months) radiation cystitis in patients with localized prostate cancer.

### Secondary Objectives

Our secondary objectives are to determine biological markers of the severity of early radiation cystitis and to describe changes in urinary and fecal microbiota in accordance with the severity of early radiation cystitis.

### Exploratory Objectives

Our exploratory objectives are to describe the biological markers of severity of late radiation cystitis (>6 months) and to describe the lipidome and metabolome changes in accordance with the precocity of radiation cystitis.

## Methods

### Study Design

The Radiotoxicity Bladder Biomarkers (RABBIO) study is an interventional, prospective, single-arm, exploratory study aimed to identify factors potentially related to radiation-induced bladder toxicity in patients with localized prostate cancer treated with radiotherapy. This study will be conducted at the Bégin Military Teaching Hospital (Saint-Mandé, France).

### Ethical Considerations

The study has been validated by national ethics committees (unique protocol ID number 2021-A03196-35; favorable opinion of the South Mediterranean Committee for the Protection of Persons I 03/02/2022) and the French Data Protection Agency. The study is registered on ClinicalTrials.gov (NCT05246774). The survey complies with the tenets of the Declaration of Helsinki. All patients will be informed that the data collected may be used for research purposes, and will be asked to provide their written consent.

### Patient Population

The eligibility criteria for the RABBIO study are listed in Textbox 1.

Inclusion and exclusion criteria.
**Inclusion criteria:**
Collection of signed informed consent forms prior to participation in the studyPatients are aged ≥18 years at the time of selectionHistologically confirmed adenocarcinoma of the prostate is presentLocalized adenocarcinoma of the prostate according to the D'Amico classification is presentPatients are eligible for external radiotherapy or brachytherapyPatients are affiliated to a social security schemePatients are able to communicate well, understand, and comply with the requirements of the study according to the physician investigatorPatient has a smartphone or computer to use the Cureety platform
**Exclusion criteria:**
Patients have advanced or metastatic prostate cancerPatients are receiving preirradiation hormone therapyPatients have bladder or urethral cancer or a history of cancerPrevious urinary tract surgery (bladder augmentation or cystectomy)Patients are participating in an interventional clinical studyPatients have a history of pelvic irradiation

### Participants’ Calendar

Early symptoms of radiation cystitis are likely to occur during treatment or within 3 months of radiotherapy in approximately half of the patients [7]. Therefore, we decided to follow the early manifestations of radiation-induced bladder toxicity for 3 months (weeks 1 to 12) and to attempt to identify biomarkers that are potentially related to acute radiation cystitis symptomatology.

Late manifestations of bladder damage secondary to pelvic irradiation may occur after a minimum of 3 months or even several years after the end of irradiation [4,6]. It has been established that the average delay in the occurrence of these complications is 2 years [6]. However, the pathophysiological changes between the end of radiation and the occurrence of late complications are not known. In this study, we aim to, as an exploratory objective, determine biomarkers that may be predictive of late radiation cystitis by quantifying biomarkers at week 52.

The design of RABBIO study is shown in Figure 1.

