##### Monitoring of Radiotherapy Adverse Events and Patient-Reported Quality of Life Using the Cureety Platform

The Cureety platform will allow remote monitoring of urinary symptoms reported by patients in accordance with the CTCAE (Common Terminology Criteria for Adverse Events) guidelines [22] (Multimedia Appendix 1). 

Patients will complete the Pelvic Radiation Adverse Events Questionnaire at the inclusion visit, then once a week for 3 months (weeks 1 to 12), and then at the end-of-study visit (week 52). The questionnaire includes the following items: fatigue, nausea or vomiting, pain, hematuria, frequency of urination (pollakiuria), urinary burning, diarrhea, fecal incontinence, urinary leakage, blood in the stool (rectorrhagia), constipation, weight loss, and dysuria.

On receipt of the questionnaires on the adverse effects of radiation, an artificial intelligence algorithm will classify patients into 1 of 4 states: correct condition (green), fragile state (yellow), condition to monitor (orange), and critical condition (red; Figure 2). The patient will receive therapeutic advice depending on the severity of the symptoms. If the patient’s condition changes to orange (watch) or red (critical), rapid management of the patient will be activated by the health care team (Figure 2).

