### Statistical Analysis

As this is a pilot exploratory study, the sample size was not based on a statistical argument. As the variability and evolution of biomarkers over time and the history of the disease are not known, and in order to explore the links between biomarkers and the occurrence of radiation cystitis, based on the hypothesis that half of the patients initially included will develop cystitis, a sample size of 60 individuals—including 30 individuals with cystitis and 30 individuals without cystitis—seems acceptable. Statistical analysis will be carried out using SAS (version 9.4; SAS Institute Inc) and R (The R Foundation) [31].

Basic statistics will be used for continuous variables n, missing n (if applicable), mean, type of deviation, median, first and third quartiles, and minimum and maximum values, and for categorical variables, we will use frequency and percentage values.

The type I error (α, 2-sided) will be 5%. The type II error (β) will be 20%; that is, a power (1-β) of 80% will be considered.

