### End Points and Evaluation

The primary end point will indicate variations in the expression of the 33 inflammatory and remodeling biomarkers assessed using the MILLIPLEX MAP technique for the analysis of circulating markers and flow cytometry for the analysis of the immune population at the 4th and 12th weeks after the start of irradiation. 

The secondary endpoints will indicate symptoms and the severity of early radiation cystitis through electronic reporting of patient-reported outcomes–CTCAE self-assessment questionnaires at inclusion and once a week during weeks 1 to 12. We will also be interested in voiding disorders, quality of life, and physical activity assessed using the IPSS, FACT-P, and IPAQ self-assessment questionnaires at inclusion and at weeks 4 and 12. Furthermore, we will characterize the composition of the urinary and fecal microbiota via 16S ribosomal RNA sequencing at baseline and at weeks 4 and 12.

Finally, we shall explore the eligibility criteria, and then at week 52, the symptoms and severity of cystitis will be assessed through electronic reporting of patient-reported outcomes–CTCAE self-assessment questionnaires, and voiding disorders, quality of life, and physical activity will be assessed with the IPSS, FACT-P, and IPAQ self-assessment questionnaires, and then the composition of the urinary and fecal microbiota will be characterized through 16S ribosomal RNA sequencing. We will analyze serum and urine lipidome and metabolomes at weeks 4, 12, and 52.

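### The 50% cystitis rate behind the expected 30/30 split covers treatment plus 3 months after it, while weekly symptom collection stops at week 12, apparently counted from the start of irradiation

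*Protocol article*

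**What the plan says.** - **Window and rate.** Background and Rationale says: "Early symptoms of radiation cystitis may occur during treatment and up to 3 months after the end of radiotherapy", and attaches the rate to those symptoms: "with an estimated all grade incidence of nearly 50% after pelvic irradiation". Participants' Calendar repeats both: "Early symptoms of radiation cystitis are likely to occur during treatment or within 3 months of radiotherapy in approximately half of the patients".
- **Follow-up.** Participants' Calendar draws its follow-up period directly from that statement: "we decided to follow the early manifestations of radiation-induced bladder toxicity for 3 months (weeks 1 to 12".
- **Questionnaires.** The adverse event questionnaire is completed at inclusion, "then once a week for 3 months (weeks 1 to 12), and then at the end-of-study visit (week 52". The symptom score and quality-of-life questionnaires are due at inclusion and weeks 4, 12 and 52.
- **Anchor of the week count.** End Points and Evaluation sets the biomarker assessments "at the 4th and 12th weeks after the start of irradiation". No anchor is written out for the questionnaires.
- **Definition.** The Main Objective calls cystitis early if it occurs in under 3 months, without saying from when.
- **Sample size.** Statistical Analysis expects 30 cases and 30 non-cases among 60 men, "based on the hypothesis that half of the patients initially included will develop cystitis". It also says that the size has no statistical justification.

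**The concern.** The follow-up period is presented as a consequence of the acute window, but the treatment time has dropped out on the way. A window of treatment plus 3 months has become 3 months in total. The 50% rate, which belongs to the longer window, is then used to predict how many cases the shorter one will show.

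Two things are at stake. The number of observed cases may be lower than planned. The comparison group may also contain men whose acute cystitis began after the last weekly questionnaire, which would pull marker differences toward zero. Both bear on the main objective, since whether a man had early cystitis is what the markers are related to. Symptoms that were never collected cannot be recovered in the analysis. The size of the loss also varies with treatment length, so case detection may be tied to the radiation regimen.

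**Working it through.** **The plan's own figure.** 60 × 0.50 = 30 cases and 30 non-cases. This reproduces, as an expectation.

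**The gap.** Let L be the course length in weeks. The article does not give L and admits both external radiotherapy and brachytherapy, so the values below are assumptions. Three months is taken as 12 weeks (the article's own equation) to 13 weeks (the calendar).

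Acute window = L + 12 to L + 13 weeks from the start. Observed = 12 weeks. Unobserved = L to L + 1 weeks.

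| L (assumed) | Window ends at week | Unobserved weeks | Share of window observed |
|---|---|---|---|
| near 0 | 12–13 | 0–1 | 12/13 = 92% to 100% |
| 4 | 16–17 | 4–5 | 12/17 = 71% to 12/16 = 75% |
| 8 | 20–21 | 8–9 | 12/21 = 57% to 12/20 = 60% |

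**Does the anchor matter?** If the questionnaire weeks were counted from the end of treatment instead, they would cover the 3 months afterwards but miss the treatment period. On either count, 12 weeks cannot contain treatment plus 3 months unless L is close to zero.

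**Effect on the split.** Let f be the share of true acute cases that start after week 12. The article gives no basis for f. If such men are treated as non-cases:

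- observed cases = 30(1 − f);
- observed non-cases = 30(1 + f);
- share of non-cases who are really cases = f/(1 + f);
- a true mean difference d shrinks to d/(1 + f).

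| f (assumed) | Split | True cases among non-cases | Difference retained |
|---|---|---|---|
| 10% | 27/33 | 3/33 = 9% | 1/1.1 = 91% |
| 20% | 24/36 | 6/36 = 17% | 1/1.2 = 83% |
| 30% | 21/39 | 9/39 = 23% | 1/1.3 = 77% |

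**Scale in terms of power (illustration only).** With 30 per group, two-sided 5% and 80% power, the detectable difference is (1.960 + 0.842) × √(2/30) = 0.723 SD. For a true difference of that size, power = Φ(d/(1 + f) ÷ √(1/cases + 1/non-cases) − 1.960). At f = 20%, this is 0.603 ÷ √(1/24 + 1/36) − 1.960 = 0.33, giving 63%. At f = 10% and 30% it is 72% and 54%. Imbalance alone would leave 80%, 78% and 76% for f = 10%, 20% and 30%, so nearly all of the loss comes from dilution of the comparison group.

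**Chance variation.** Even with complete follow-up, a binomial count with 60 men and probability 0.5 lies between 23 and 37 about 95% of the time, and equals 30 only 10% of the time.

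**The case against.** The strongest reply is that the Background sentence is cited literature, not the study's definition. The study's own definition, in the Main Objective, has no anchor, and weeks 1 to 12 do not contradict it. This stands: a reader might infer that the protocol defines early cystitis up to 3 months after the end of radiotherapy, and it does not. But the 50% rate still comes from the longer window, so the mismatch between rate and follow-up remains.

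Other parts of the reply also hold:

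- The start anchor is explicit only for the sample visits, and the design figure is not available. The abstract places the questionnaires between those visits, so a shared calendar is the natural reading, but it is an inference.
- No rule says how a man with symptoms after week 12 is classified. He becomes a non-case by default, not by a stated rule.
- A reader might conclude that the 30/30 split will not be reached. That depends on onset timing, which is not given. If most symptoms begin during treatment, the loss is small. A count of 24 also lies within ordinary chance variation around 30, although late onset would shift the centre of that range downward and chance does not.
- Assuming that onset is spread evenly over the window would give larger losses, but that is one arbitrary pattern and not an upper bound.
- The pilot's size has no statistical basis and no effect size is stated, so no power guarantee is broken.
- Radiation regimen is recorded, so differences in detection by regimen can be examined. The missing symptoms themselves cannot be restored.
- Ending symptom follow-up at the last early sample is a defensible choice. It then needs a rate that matches that period.

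**Conclusion.** The point holds in a limited form. A rate for treatment plus 3 months is applied to a follow-up that, on the natural reading of the calendar, ends 12 weeks after treatment starts, and no symptoms are collected between weeks 12 and 52. The direction is clear: a shorter window cannot raise the expected number of cases. The size is not known. The unobserved part is about 4 to 9 weeks for assumed courses of 4 to 8 weeks, and close to zero for brachytherapy or very short courses. The expected split moves to 27/33, 24/36 or 21/39 if 10%, 20% or 30% of cases start after week 12. The documents support saying that observed cases may fall below 30 and that the comparison group may contain undetected acute cases. They do not show that either will happen to a material degree. For a single-arm exploratory pilot this is of moderate severity.

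**What to change.** State in the Main Objective what the 3 months are counted from, and state the same anchor for the questionnaires. Then do one of the following.

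1. **Preferred:** continue the existing weekly electronic questionnaire until 3 months after each patient's last radiation session, and define early cystitis on that window. This costs about 4 to 9 more short questionnaires per patient on a fractionated course (with the course lengths assumed above), few or none for very short treatments, and a brief amendment. No visit or sample is added. A limit remains: symptoms that start after week 12 would have no concurrent early biomarker sample.
2. **Otherwise:** define the outcome as onset by week 12 from the start of irradiation, and replace the 50% and 30/30 figures with a lower expected case number for that window. This costs only a change of wording, but narrows what the study can say about acute cystitis.
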